**Extension of mother groups and follow-up assessment**

We propose to extend the mother groups component of the study to increase exposure to the parenting component of the study. Preliminary results indicated encouraging results from the mothers’ group component in terms of behavior change and engagement in the child development of their children. Mothers would like to continue the intervention and we propose

to formally support this extension. At the end of the extended period, we propose to re-assess the

cognitive and socio-emotional development of children in the intervention component. This will

allow us to measure in a more precise way and also after increased exposure to the program, both

of which will increase the power to detect a change in cognitive and socioemotional development. We will also re-assess parenting practices to observe any long-term follow-up in terms of parenting practices and engagement. The results from the first year indicate that Intergrowth might not be the best assessment tool, and we propose therefore to use the gold standard, the BSID-III.

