**Specific objective #6:** To determine the relationship between the 5 selected health facilities’ quality (measured and perceived) and parents’ use of services for malnourished children. Both perceived and parents’ use of services will be collected via questions collected on baseline data regarding satisfaction to health facility services. Facility quality will be determined by a structured KII with health facility staff. Questions for health facility staff will focus on:

- Health worker knowledge on treatment of malnourished children
- Health facility screening procedures
- Quality of nutrition services
- Audit of clinic resources

**Specific Objective #7:** To assess the usual diet of 6-12 month old infants. We will use a form that utilizes the 24-hour recall method to measure quantities and types of foods consumed by the child in the past 24-hours as reported by the mother.

- Measure by 24-hour recall, time and food or beverage consumed
- Aid of measuring cups, food pictures and diagrams

**Specific Objective #8:** Describe and document the perceptions of mothers on mother groups, as well as any behavioral changes in parenting or in mother support networks resulting from participation in mother groups.

This will be done through focus group discussions and analyzed with qualitative analysis methods.

**Specific Objective #9: A**ssess parenting behavior prior to the start of the mothers’ group extension, in April 2016.

We will visit all study households (intervention and control) in April 2016 and collect information on a short set of parenting behaviors. We have attached the instrument we will use. The parenting behaviors we will assess are the same as those assessed during previous household surveys for this study. We will also obtain a new informed consent form from all study households at this visit.

**Specific Objective #10:** Assess the impact on parenting practices and primary outcomes after extending the mother groups component for an additional period of time (7 months).

While the assessment of cognitive development at less than 2 years of age is very difficult and is and not-precise, the assessment closer to 3 years-old can be more reliable. We will continue the mothers’ groups component of the study (parenting) for 7 additional months, then re-assess the cognitive development of the children as well as parenting practices.

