## Sample Size Calculations

The study is designed to detect increases in standardized child development scores of 0.5 standard deviations with power = 0.9. The main assumptions underlying this calculation are an average group size of 20 children in each of the 30 zones, and an intra-class correlation coefficient of 0.1 (a design effect of 2.9). Similarly, the study is powered to detect an increase in height-for-age z-scores of 0.5 standard deviations in the intervention arm relative to the control arm. We aim to enroll 250 children in each study arm for a total sample of 500 children. In order to account for lost to follow-up, we aim to recruit up to 5% additional children per study arm (262 per arm).

For the year two follow-up assessment, we are powered to detect an increase in standardized child development scores, as measured by the BSID-III, of 0.3 standard deviations with power 0.8.

Sample size for health facility surveys and feeding centers is seven. There will be 10 health workers interviewed (assuming 2 per health facility), 5 national, provincial and district level nutritionists or clinical-care specialists and the feeding sample size for assessment of dietary intake will be all willing and enrolled intervention children (estimate 275).

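### The year-two developmental re-assessment is described for intervention children, contradicting the impact objective, and the year-two power figure does not follow from the stated ICC even with both arms tested

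*Protocol*

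**What the plan says.** Protocol, Extension of mother groups and follow-up assessment: at the end of the extension the team proposes to re-assess the "cognitive and socio-emotional development of children in the intervention component". The instrument changes to the BSID-III. Of more precise measurement and longer exposure, the section says both "of which will increase the power to detect a change in cognitive and socioemotional development".

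Protocol, Specific objectives: Objective 10 is to "Assess the impact on parenting practices and primary outcomes after extending the mother groups component" by 7 months, and "then re-assess the cognitive development of the children as well as parenting practices". It does not say which arm. Objective 9, the parenting visit before the extension, does say: "We will visit all study households (intervention and control) in April 2016".

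Protocol, Analysis for Objective 10: stunting and the BSID-III score are the two year-two primary outcomes. No comparator is named.

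Protocol, Sample Size Calculations: "For the year two follow-up assessment, we are powered to detect an increase in standardized child development scores", with an effect of 0.3 SD on the BSID-III and power 0.8. Again no comparator is named.

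Protocol, Study design: a two-arm cluster-randomised trial.

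**The concern.** Only one sentence in the Protocol says which children take the year-two developmental test, and it names the intervention side. An impact estimate needs control children measured at the same time with the same tool. A field team following that sentence would return from the November 2016 round with no control BSID-III scores. No later analysis plan could repair this, because the data would not exist.

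What is at stake is the randomised comparison for development at year two. Under Objective 10, the Protocol itself regards assessment closer to age three as more reliable than assessment before age two.

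**Working it through.** **Part 1. Who is measured, and can anything else supply the comparison?**

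- Endline Assessment (year one): all children, so both arms. Recruitment and baseline survey confirms that control households have the endline development assessment.
- Objective 9 visit (April 2016): both arms, but only parenting behaviours, and before the extension. It gives no developmental score and no post-extension comparison.
- Assessment of dietary intake: intervention children only, by design. The Protocol therefore does plan some one-arm measurements, and a restrictive reading of the year-two sentence is reasonable.
- Year-two developmental test: intervention children named, control children not mentioned anywhere.
- Year-two stunting and parenting practices: no arm named, so no restriction is stated.

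A before-after contrast within the intervention arm cannot stand in for the controls. Data capture/paper storage gives the neurocognitive assessment at endline only, so there is no baseline score. The year-one tool was INTERGROWTH and the year-two tool is the BSID-III. The Time Frame puts the two rounds at October 2015 and November 2016, about 13 months apart, so programme effect, ageing and change of tool cannot be separated.

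**Part 2. Does the year-two power hold if both arms are tested?**

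Inputs from Sample Size Calculations: 250 children per arm, 30 zones, 20 children per zone, ICC 0.1, design effect 2.9. No alpha is stated; two-sided 5% is assumed. Because 20 × 30 = 600 but the target is 500, I also use 500/30 = 16.7 children per zone.

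Formulas: design effect DE = 1 + (m − 1) × ICC; effective size per arm n_eff = 250/DE; power = Φ(d × √(n_eff/2) − 1.96).

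*Year one first (0.5 SD, stated power 0.9).* DE = 1 + 19 × 0.1 = 2.9. n_eff = 250/2.9 = 86.2. 0.5 × √43.1 = 3.28. Φ(3.28 − 1.96) = 0.907. The stated figure is reproduced, as a two-arm comparison.

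*Year two (0.3 SD, stated power 0.8), same inputs.*

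- DE 2.9: 0.3 × √43.1 = 1.97; Φ(0.01) = 0.50.
- DE = 1 + 15.67 × 0.1 = 2.57: n_eff = 97.4; 0.3 × √48.7 = 2.09; Φ(0.13) = 0.55.
- Most generous size, 300 per arm (15 zones × 20) with DE 2.9: n_eff = 103.4; power 0.58.
- With a t reference on 28 degrees of freedom the three values are 0.48, 0.53 and 0.55.

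*What would be needed for 0.8.* Without clustering, 2 × (1.96 + 0.84)² / 0.3² gives 175 per arm. Multiplied by the design effect, that is about 449 (DE 2.57) to 508 (DE 2.9) per arm. With 250 per arm, DE would have to fall to about 1.43, which means an ICC of about 0.028 (16.7 per zone) or 0.023 (20 per zone). Alternatively, covariates would have to remove about 44% to 51% of the variance. Ignoring clustering altogether gives 0.92.

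*Detectable difference at power 0.8 with 250 per arm.* (1.96 + 0.84) × √(2/n_eff) = 0.43 SD (DE 2.9) or 0.40 SD (DE 2.57).

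**The case against.** The best case for the plan is that this is loose wording and that both arms were always meant. The sentence does not say only, and does not use the word arm. In the same section, component otherwise means part of the programme. Objective 10 speaks of impact and of the children without restriction. The general model under Data analysis uses random assignment to predict each outcome. April 2016 brings a visit and new consent in both arms, although the Informed Consent section ties that consent to the parenting assessment, so it does not show that controls are tested in November.

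Much of this stands. A reader might infer that the sponsor has decided to drop the controls at year two. The documents do not support that; an internal contradiction is the likelier explanation. A reader might also infer that Objective 10 as a whole loses its comparison. That goes too far as well, since nothing restricts stunting or parenting practices to one arm.

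What does not stand is the idea that no change is needed. The one procedural sentence on the developmental test still conflicts with the objective it serves, and elsewhere the Protocol names both arms when it means both.

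On power, the year-two sentence gives no ICC, alpha or covariate adjustment of its own, so a basis for 0.8 may exist. It is not in the Protocol, and the only ICC given does not produce it.

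**Conclusion.** The Protocol contradicts itself on who takes the year-two developmental test. If the sentence is followed, the BSID-III outcome has no randomised comparator, and within-arm change cannot be read as programme effect. The point is limited to cognitive and socio-emotional development.

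With one arm measured, power for a between-arm effect is undefined; it would be wrong to report it as zero. That the year-two claim concerns a between-arm difference is itself an inference, from the two-arm design and the year-one calculation. A one-sample test of 250 intervention children with design effect 2.9 happens to give 0.795. A reader might take this as the source of the 0.8, but the Protocol says nothing of the kind and the match may be coincidence.

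If both arms are tested, power for 0.3 SD is about 0.50 to 0.55 rather than 0.8. This rests on 250 per arm with no losses, ICC 0.1 carried over from year one, no covariate adjustment and two-sided 5% alpha.

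**What to change.** 1. In Extension of mother groups and follow-up assessment, state that children in both intervention and control zones are re-assessed with the BSID-III. Under Analysis for Objective 10, state that the effect is the between-arm difference, by randomised zone. Bring Objective 10 and Sample Size Calculations into line.
2. If control children will not be tested, restate the year-two development aim as descriptive and withdraw the year-two power claim.
3. If both arms are tested, either restate the year-two power (about 0.50 to 0.55 for 0.3 SD, or 0.8 for about 0.40 to 0.43 SD) or give the ICC, alpha and covariate assumptions that yield 0.8.

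Cost: a few sentences and one recalculation if both arms are already intended. If they are not, the choice is between assessing the control arm as well (up to about 250 children at the enrolment target) and giving up the year-two impact claim for development.

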## Assessment of malnutrition screening

To obtain a qualitative overview of how the national malnutrition guidelines are being implemented at the provincial and district levels, we plan to conduct a survey interviewing nutrition and/or clinical care specialists at different levels of the health system (district, province, and national).

To assess the quality of nutrition services at facilities, we propose to conduct structured interviews with the clinic staff (e.g. to assess health worker knowledge of malnutrition treatment, health facility screening procedures, and management for malnutrition) and conduct an audit of clinic resources, (e.g., the number of people that have access to the facility, staffing levels, equipment, and availability of RUTF).

To understand parents’ perceptions and use of services for a potentially malnourished child, we will use household interview data being collected as part of the study baseline procedures (e.g. if your child is stunted or not gaining weight, what services are available or what will you do; do you know of local or home services available?).

## Assessment of health facility current practices and standards of care

Health facility assessment: Participants will be nurses certified in treatment of severe acute malnutrition or in–charges (managers) of participating health facilities which will includes health centers, both in the public and mission run.

Health worker interviews: The participants will be clinical staff providing malnutrition treatment in the participating health facilities on the day of the survey.

- - 1. **Assessment of dietary intake**

During a bi-weekly visit, the CDAs will perform a one time 24-hour recall to assess the food consumption of all intervention children in five selected health facilities. CDAs will be trained on interviewing techniques, how to elicit detained descriptions of food and beverage items, and how to estimate and record and record portion size. Portion sizes will be estimated via modeling clay molded into the correct size and shape of the food, portion-sized photographs of foods and standard measuring cups.

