## Study interventions

Communities selected for the intervention arm will benefit from a new cadre of health workers, which will be recruited and trained for the sole purpose of monitoring and supporting all aspects of child development under the age of 2. The newly trained health workers will bear the title of “child development agents” (CDA) and will be community-based. A total of five CDAs will be trained and employed for the project period; their sole responsibility will be to support targeted children and their caregivers with the interventions outlined below. We will ask for community recommendations for the selection of CDAs with the requirement that they have some previous experience in health-related activities and ability to read and write in both English and Tonga, the local tribal language. The CDAs will be employed by the project and work full-time. Each CDA will be responsible for approximately 50 intervention children across three health zones. **CDAs will visit all intervention children on a bi-weekly basis**. In total, CDAs are expected to conduct 100 household visits per month (50 children times two visits each); this will mean that they will each do about five visits per day. **The home visits will have two fundamental functions:**

1. **Ensuring treatment of malnutrition and acute infections**. CDAs will monitor children’s growth using mid-upper arm circumference (MUAC) measurements, if they identify children that have moderate acute malnutrition (defined as absence of edema and MUAC <12.5 and ≥11.5 cm), they will provide supplemental information to the caregiver on how to improve the child’s diet. If the CDAs identify children with severe acute malnutrition (defined MUAC <11.5 cm without edema or MUAC of <11.0 – 12.5 cm with pedal edema), they will be advised to immediately refer the child to the nearest health facility for further evaluation and management. Similarly, CDAs will inquire about symptoms of malaria, acute diarrhea or pneumonia, and instruct parents to seek treatment at the nearest health facility as needed.

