## Eligibility Criteria

Inclusion

- Children aged 6-12 months in the catchment areas of the five selected health facilities in Southern Province will be eligible to participate
- Child’s primary caregiver must be 15 years or older
- Child’s primary caregiver must be a female (because the participants in the women’s group may feel uncomfortable discussing certain issues if a man is present)
- Health workers working at the five health centers where the study is taking place
- District and provincial level nutritionists or clinical care specialists

Exclusion

- Caregivers who are unwilling to provide informed consent
- Families that plan to move from their health center catchment zone during the twelve month period of the study
- Health workers, nutritionists, or clinical care specialists who refuse to provide informed consent

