**Analysis of objectives 5-7**

Hand written notes will be taken by the interviewer in addition to an audio recording of the interview. The notes will then be coded for common themes and outliers. For analysis of KII data, we will focus on individual views and will, where relevant, look at the proportion of total respondents who report particular views. To the greatest degree possible, this analysis will begin during data collection or shortly after the KIIs are completed in order to permit participation in the analysis by the interviewers who conducted the KIIs and therefore who will be most familiar with the information collected.

At the beginning of the study, a one time, one-day dietary intake will be collected by each CDA prompting the mother or caregiver to complete a 24-hour food recall of their child’s food and drink intake as described in the GAIN working Paper Series. (43) Descriptive frequencies of food intake and proportions of food groups represented will be examined and comparative analysis to WHO guidelines will be performed.

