# Time Frame

| Development of intervention materials and BU IRB/Zambian ethics committee approvals | Sept 2013 – April 2014 |
| --- | --- |
| Surveyor and CDA recruitment and training | April 2014 |
| Pre-testing data collection instruments, enrollment and baseline survey | May 2014 |
| Intervention rollout | September 2014 |
| Endline evaluation | October 2015 |
| Data analysis | November 2015 |
| Year 1 report and data dissemination | December 2015 |
| Parenting assessment | April 2016 |
| Mothers group extension | April 2016 |
| Year 2 (follow-up) evaluation | November 2016 |

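### Objective 7 concerns infants aged 6-12 months, but the single diet recall is tied to an unspecified fortnightly visit that, on the protocol's timetable, most children reach after 12 months of age

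*Protocol*

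**What the plan says.** Under Specific objectives, Objective 7 reads "To assess the usual diet of 6-12 month old infants", using a 24-hour recall reported by the mother. The Eligibility Criteria set the same age range, but at entry: "Children aged 6-12 months in the catchment areas of the five selected health facilities in Southern Province will be eligible to participate".

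Two places time the recall. The dietary-intake paragraph (within the section on health facility practices and standards of care) says "During a bi-weekly visit, the CDAs will perform a one time 24-hour recall to assess the food consumption of all intervention children". The section Analysis of objectives 5-7 says "At the beginning of the study, a one time, one-day dietary intake will be collected by each CDA" and plans descriptive frequencies, food-group proportions and a comparison with WHO guidelines.

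Fortnightly visits take place only in intervention zones. The recall is not among the baseline survey items (a) to (g) listed under Recruitment and baseline survey. The Time Frame table has "Pre-testing data collection instruments, enrollment and baseline survey | May 2014" and "Intervention rollout | September 2014".

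Sample Size Calculations gives the recall sample as "all willing and enrolled intervention children (estimate 275"), next to a target of 250 children per arm and a recruitment figure of 262 per arm.

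**The concern.** The objective fixes an age range, and the children are inside it when they enrol. The recall, however, is attached to an activity that begins after enrolment, and nothing says which visit or up to what age. If the gap is several months, most of the cohort will have left the range before the first possible recall.

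Diet changes quickly around the first birthday, and the planned output is a comparison with WHO guidelines. At stake is whether food frequencies from mostly older children, possibly collected after some caregivers have had nutrition advice, would be reported as the usual diet of infants aged 6-12 months.

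**Working it through.** The protocol gives no age at recall, so there is no stated figure to reproduce. The check is calendar arithmetic on the protocol's own dates.

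**Inputs**
- Age at enrolment: 6-12 months (Eligibility Criteria).
- Enrolment and baseline: May 2014. Rollout: September 2014. Endline: October 2015 (Time Frame).
- Routine health and nutrition visits last 12 months (Routine visits in intervention clusters).
- Parenting groups, whose curriculum includes nutrition, start around month 3 of the intervention (same section).
- Assumption, not in the protocol: ages at enrolment are uniform over the range.

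**Age at the first fortnightly visit, on the timetable**
- Lag = September 2014 − May 2014 = 4 months.
- Age = (6 to 12) + 4 = 10 to 16 months.
- Share still aged 12 months or younger = (6 − lag)/6 = 2/6 ≈ 33%. If 12 months is read as completed months, so that ages at entry span 6.0 to 12.99, the share is (7 − 4)/7 ≈ 43%.

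**Sensitivity to the lag**

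| Lag (months) | Age at first visit (months) | Share still in range, (6 − lag)/6 |
|---|---|---|
| 0 | 6-12 | 100% |
| 1 | 7-13 | 83% |
| 2 | 8-14 | 67% |
| 3 | 9-15 | 50% |
| 4 | 10-16 | 33% |

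The lag has to be varied because the protocol does not settle it:
- The routine-visits section starts visits once enrolment and the baseline survey are complete, and states no gap.
- The Endline Assessment is set at twelve months after enrolment. May 2014 to October 2015 is 17 months. Counting back 12 months from October 2015 gives enrolment around October 2014, which is next to rollout and implies essentially no lag.
- September 2014 to October 2015 is 13 months, which also fits enrolment close to rollout.

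**Later recalls**

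The figures above are for the earliest fortnightly visit. Any visit in the 12 months is allowed as the text stands.
- Three months into the intervention, when group sessions are expected to begin, children would be 10 + 3 to 16 + 3 = 13-19 months on the timetable. None would be in range.
- With no lag they would be 9-15 months, and about half would be in range.
- At the end of the visit period, on the timetable, they would be 10 + 12 to 16 + 12 = 22-28 months.

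**Recall sample**
- 275/250 = 1.10 and 275/262 ≈ 1.05. The estimate is about 5% to 10% above the per-arm figures in the same section.

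**The case against.** The best defence is that an early fortnightly visit can satisfy both the procedure and the analysis section: if visits follow directly on baseline, a recall at the first one is at the beginning of the study and the children are still 6-12 months old. The four-month gap comes from the timetable alone, and the endline rule points the other way. This stands as far as it goes. It means that 10-16 months is a figure on the timetable's dates and not an established fact. It does not settle the matter, because the text does not specify the first visit and any lag moves some children out of range.

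A reader might infer three stronger things that the protocol does not support.

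- **That the recall describes advised households.** Individual diet advice is conditional. For a child with moderate acute malnutrition, "they will provide supplemental information to the caregiver on how to improve the child’s diet", and the routine-visits section likewise ties dietary suggestions to malnutrition. Group nutrition content comes only after about month 3. A recall at the first visit would precede most of this. What can be said is that some caregivers may have had advice by a later recall.
- **That leaving out control households is an error.** The procedure and the sample-size section both limit the recall to intervention children. The objective is descriptive, no arm comparison is planned for it, and zones are randomised. Child diet diversity at year two can be compared between randomised arms without a baseline value. Control-arm recalls would be an addition, not a correction.
- **That 275 shows the sample is wrong.** It is labelled an estimate. Five facilities with 100-150 eligible children each would give 250-375 per arm, so it is not implausible. It simply does not match the neighbouring figures.

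It is also fair to say that this version of the protocol already refers to first-year results, so a change to the baseline visit may no longer be possible.

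**Conclusion.** The point holds as an unreconciled timing rule. Objective 7, the dietary-intake procedure, the analysis section and the Time Frame do not together ensure that the recall is taken at 6-12 months.

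On the timetable's dates, about two thirds of children would be past 12 months at the first fortnightly visit (57% if 12 means completed months). Across the lags the protocol permits, the share past 12 months at that visit runs from none to about two thirds, and it is higher for any later visit. These shares rest on uniform ages at enrolment and on the first visit coinciding with rollout.

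Severity is minor. The consequence is a mislabelled descriptive result; no primary or secondary comparison between arms is affected.

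**What to change.** Choose one time for the recall and state it consistently in Objective 7, the dietary-intake procedure, the analysis section and the Time Frame. The simplest choice is the existing baseline survey contact, in intervention children, before the first programme visit. All children are then 6-12 months old and no programme advice has been given. The cost is a longer baseline visit, since the recall uses clay models, photographs and measuring cups; no extra visit is needed.

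If baseline has already passed, the remedy lies in analysis and wording:
- Derive and report each child's age at recall.
- Limit the 6-12 month description and the corresponding WHO comparison to children in that range, and give their number.
- Otherwise restate Objective 7 as the diet of intervention-arm children at their actual ages after programme start.

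The estimate of 275 should also be aligned with the 250-262 per arm in the same section, or its source stated. Recalls in control households are optional.
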